### Secondary outcomes

Cardiac self-efficacy refers to an individual’s confidence in managing cardiovascular disease. It will be measured using the Cardiac Self-efficacy Scale (CSES), originally developed by Sullivan [64]. The 13 item questionnaire consists of two subscales to measure one’s self-efficacy in maintaining function and to control symptoms. The CSES uses a 5-point Likert scale with a higher score indicate higher self-efficacy. The original version of the CSES has good internal consistency with Cronbach’s alpha of 0.90 and 0.87 for the subscales. The CSES has been translated and validated among Chinese cardiac patients with internal consistency of 0.926. The construct validity of the C-CSES was established with significantly moderate correlations General Self-efficacy Scale (r = 0.47, *p* < 0.001) [65].

Health-related quality of life will be measured by the MacNew Heart Disease health related quality of life questionnaire (HRQoL), which evaluates how an individual’s emotional, physical and social well-being are affected by CHD and its treatment. It has 27 items scored from 1 (low HRQoL) to 7 (high HRQoL) with internal consistency and intraclass correlation coefficients≥0.73 [66]. It has been translated and validated among Chinese CHD populations with intraclass correlation coefficient ranging from 0.88–0.93 [67].

Psychological status of participants will be measured by the Depression Anxiety Stress Scale 21 (DASS-21) consisting of 21 items in three domains: depression, anxiety and stress [68]. Respondents are required to indicate the presence of the symptom(s) over the past week on a 4-point Likert scale scoring from 0 to 3 with higher scores indicate more severe symptoms. This instrument has well-established psychometric properties in reliably measuring depression, anxiety and stress (Cronbach’s alpha of 0.91, 0.84 and 0.90 respectively). The DASS-21 correlated strongly with hospital anxiety and depression scale both for anxiety (r = 0.88) and depression (r = 0.93) [69]. The DASS-21 has been translated and validated among Chinese with Cronbach’s alpha≥0.80 [70, 71].

The cardiac physiological risk parameters include body mass index (BMI), blood pressure and waist circumference. Body weight and height will be examined using the same equipment (Xiheng, RGZ-120-RT, China) with participants in light clothing, shoes removed, upright posture and looking straight ahead. Blood pressure will be measured in a sitting position after participants have rested for 10 min (Omron HEM-7124, Japan). Waist circumference will be measured using a flexible tape measure at umbilicus level.

The unplanned health services use is defined as unplanned cardiac-related hospital readmissions, emergency department visits and re-vascularization. Because China does not have an electronic medical records system, the participants will be reminded to call the outcome assessor whenever an unplanned health services event occurs. To reduce recall bias, the outcome assessor will assess participants’ unplanned medical services use by monthly call asking about the detailed date, unit, diagnosis and related information. Survival analysis of time-to-event data will be conducted to describe the length of time from entering the program to any readmission.

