### Study sample

The study will be conducted at four cardiology units of Tongji Hospital, Wuhan, China where CHD patients are treated conservatively with percutaneous coronary intervention (PCI) or medication and discharged under stable medication regimen. Eligibility requirements of participants are: adults aged 18 years or older; hospitalized for an initial diagnosis of CHD based on angiography or exacerbation of this condition in previously diagnosed cases; anticipated discharge to home; uses a computer and/or smartphone to access the Internet at home, reads and speaks Mandarin; minimum of primary education level; and no prescribed activity or exercise restriction. Exclusion criteria are: a diagnosis of acute psychotic disease/ life-limiting condition; absolute and relative contradictions to exercise testing and training and high risk for exercise prescription according to the American Association of Cardiovascular and Pulmonary Rehabilitation (AACVPR) guideline; and, having auditory, visual, fine motor, or ambulatory disorders.

Referring to a systematic review of studies which examined the effects of tele-cardiac rehabilitation on lifestyle behaviors, health outcomes and quality of life, the effects size on promoting healthy lifestyle is 0.42 to 1.29 so that a medium effect size of 0.5 (with 80% power and .05 significance) is conservatively adopted in this study [38]. The estimated sample size is 146, which takes into consideration an expected attrition rate of 12% based on prior studies with similar post-test time points of 6–12 weeks [31, 39]. Eligible participants will be identified by research nurses from four inpatient cardiac departments of the hospital by reviewing medical records. A second confirmation will be made with the on-site physicians. Eligible participants will then be invited to participate in this study and an information sheet will be provided. After obtaining informed consent, baseline data will be collected.

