#### Tele-care platform

In the tele-care platform, the nurse will retrieve self-monitoring data uploaded by participants and anonymously share goal attainment of group members as well as discuss their experiences and address any concerns. Reminders for uploading data will be sent to participants weekly. This platform permits participants to contact the nurse about issues or adverse changes in health. The nurse will contact each individual at weeks 2 and 4 post-discharge to assess fitness, explore difficulties, encourage progress and offer solutions. This may lead to revision of the action plan or goal adjustment. Participants will be asked to maintain password and account security, and to avoid discussing of intervention content with other patients in the hospital to avoid contamination.

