### Demographic and clinical data

Comprehensive demographic and clinical date will be collected at baseline to permit examination of factors that may influence the NeCR outcomes of participants. Demographic data (age, sex, education, marital status, employment status, living conditions and Internet use) will be collected from participants while clinical data will be retrieved from the medical record to include diagnosis, clinical presentation, documented hypertension, dyslipidemia, diabetes, any treatments being received and single/multiple vessel disease.

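### Unplanned cardiac service use is taken from participant report alone although the study hospital's records are within reach; events should be confirmed from documents in both arms

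*Protocol article*

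**What the plan says.** All places are in the protocol article.

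- **Outcome** (Secondary outcomes): "The unplanned health services use is defined as unplanned cardiac-related hospital readmissions, emergency department visits and re-vascularization".
- **Source** (same section): "Because China does not have an electronic medical records system, the participants will be reminded to call the outcome assessor" each time an event happens. The assessor also assesses "unplanned medical services use by monthly call asking about the detailed date, unit, diagnosis and related information". Both routes are participant report. No check against documents and no rule for classifying events is stated.
- **Records used elsewhere**: under Study sample, "Eligible participants will be identified by research nurses from four inpatient cardiac departments of the hospital by reviewing medical records". Under Demographic and clinical data, "clinical data will be retrieved from the medical record to include diagnosis, clinical presentation" and further items such as treatments and vessel disease.
- **Blinding** (Randomization and data collection procedure): participants know their arm. The research assistants who evaluate outcomes at T1 and T2 are described as blinded.
- **Unequal contact** (Tele-care platform, intervention arm only): "This platform permits participants to contact the nurse about issues or adverse changes in health". The nurse also contacts each participant at weeks 2 and 4.
- **Discontinuation** (Potential risks management): a participant whose health changes so that the inclusion criteria are no longer met leaves the study and is referred to care.
- **Analysis** (Data analysis): intention to treat, with a time-to-event description of unplanned service use.

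**The concern.** The outcome needs two clinical judgements: whether an event was unplanned and whether it was cardiac-related. As written, both rest on the participant's account. A visit for chest pain later judged non-cardiac may be counted or not according to how the participant describes it.

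The stated reason for relying on participants is the lack of an electronic records system. That does not explain why reported events at the study hospital, whose records the team reads for other purposes, go unconfirmed. Nor does it explain why papers are not requested for events elsewhere.

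Readmission and revascularisation could be among the outcomes least dependent on opinion in this trial. Collected this way, they become one more self-report from participants who know their arm. Only one arm has a nurse channel and extra nurse contacts, so noticing, labelling or reporting of events could differ between arms. Telephone report also stops where contact or participation stops, whereas the planned comparison is by intention to treat.

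**Working it through.** **1. The plan's own figure.** The only computed design figure is the sample size. Inputs from Study sample and Data analysis: effect size 0.5, power 80%, two-sided 5%, attrition 12%; 1:1 allocation is assumed.

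- Two-sample t-test: 63.8, rounded up to 64 per arm.
- Attrition: 64 / (1 − 0.12) = 72.7, rounded up to 73 per arm.
- Total: 2 × 73 = 146, which matches.

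This figure rests on the lifestyle effect size. Service use plays no part in it, so the present point does not touch it.

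**2. What each safeguard covers.**

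| Threat | Stated safeguard | What remains |
|---|---|---|
| Forgotten event | Event-triggered and monthly calls | Little while the participant is in contact |
| Assessor bias | Assessors described as blinded | Little, if the blind holds on the telephone |
| Wrong diagnosis or planned status | Participant is asked for date, unit and diagnosis | No verification |
| Event after loss or discontinuation | None stated | Not captured |

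**3. Record access.** Study sample and Demographic and clinical data show that the study hospital's records can be read. Secondary outcomes says that an *electronic system* is lacking, not that records are. The statements can both be true, but together they leave no stated obstacle to checking events at that hospital.

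**4. Loss of contact.** 146 × 0.12 = 17.5, about 18 participants at the planned attrition. The 12% was set for the post-test time points, so it is only a rough guide to loss from the monthly calls. Such participants lose information from the point of loss onward, not before it.

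**5. Illustration of differential capture.** The article gives no event risk and no capture rate. Assume 73 per arm, no true effect, a true risk p of 5% to 20%, and capture rates s₁ and s₀ in the two arms. Counted events are 73·p·s, and the apparent risk ratio is s₁/s₀, whatever p is.

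| p | True events per arm | Counted at 95% / 80% | Counted at 95% / 70% |
|---|---|---|---|
| 5% | 3.7 | 3.5 / 2.9 | 3.5 / 2.6 |
| 10% | 7.3 | 6.9 / 5.8 | 6.9 / 5.1 |
| 20% | 14.6 | 13.9 / 11.7 | 13.9 / 10.2 |

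- 0.95 / 0.80 = 1.19
- 0.95 / 0.70 = 1.36; reversed, 0.70 / 0.95 = 0.74
- Equal capture, for example 0.80 / 0.80 = 1.0: events are lost, but the ratio is not biased.

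The largest gap in the table is 13.9 − 10.2 = 3.7 events. Treating the counts as Poisson, the standard deviation of that difference is √(13.9 + 10.2) = 4.9. Even this gap lies within chance variation. It would shift the estimate rather than reliably produce a significant result.

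**The case against.** The case on the other side is substantial, and much of it stands.

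- **No contradiction about records.** A reader might infer that the article denies records in one place and uses them in another. The text does not support that. Screening and baseline data come from the chart of a patient who is in hospital; the outcome concerns events after discharge, possibly at other hospitals. The sentence can mean that no linked system would show care elsewhere. What stands is narrower: that reading does not explain leaving events at the study hospital unchecked.
- **Real safeguards.** Calls are event-triggered and monthly, the procedure is stated for participants generally, and the assessors are described as blinded. The Limitations section admits recall and social desirability bias for self-report measures in general. This reduces the problem but verifies no event.
- **Condensed article.** Event verification is often left to a full protocol. Here, however, the article states the method and the reason for it, so this is a stated choice and not a silence.
- **Bias by arm is not established.** A reader might infer that the arms *will* report differently. The nurse channel goes to the intervention nurse, and nothing says that it feeds the assessor's data. A difference is possible, no more.
- **Scheduled procedures.** A reader might infer that staged revascularisations will be counted. The definition excludes them; only a misreport could let one in.
- **Lost participants.** A reader might infer that they contribute nothing. In a time-to-event analysis they still contribute follow-up, and any event, up to the loss.

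**Conclusion.** The point holds as a proportionate improvement to a secondary outcome. Participant report is the only stated source for an outcome that needs two clinical judgements, and a better source is within reach for at least part of the events. Under-reporting or misclassification can occur and could differ by arm.

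Its direction and size cannot be derived from the article. The ratios of 1.19, 1.36 and 0.74 follow entirely from assumed capture rates and are not estimates of bias in this trial. With perhaps 4 to 15 true events per arm, itself an assumption, a few missed or mislabelled events can change the estimate or its direction. The primary analyses and the total of 146 are unaffected.

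**What to change.** Keep the event-triggered and monthly calls, and add the following:

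1. At T2, check the study hospital's records for every randomised participant in both arms, including those lost to contact or discontinued.
2. For reported events at other hospitals, request the discharge summary or visit slip.
3. Write down in advance what counts as unplanned and as cardiac-related. This is needed because the article states no clinical qualification for the research assistants.
4. Have the existing blinded outcome assessors classify each event against that definition from redacted documents. The on-site physicians are less suitable for this, because the article does not describe them as blinded.
5. Flag events supported by self-report only, and repeat the analysis on document-confirmed events as a sensitivity analysis.

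The cost is a modest amount of look-up work, plus consent wording that covers record access to T2. One weakness remains: events at other hospitals will be documented incompletely, and those of participants lost to contact may stay unknown. Confirmation will thus depend partly on where care was sought, which is why the sensitivity analysis is needed.

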## Methods

The study design is a single-blinded two-arm parallel randomized controlled trial comparing the effects of an eHealth CR with usual care on the behavioral and clinical outcomes of patients with CHD who are admitted for disease exacerbation.

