### Randomization and data collection procedure

Eligible patients will be invited to participate in this study and an information sheet will be provided. After obtaining informed consent, baseline data will be collected. Participants will be randomly assigned to either the intervention or control group by block randomization. Three different block sizes of 4, 6 and 8 will be used. The random number for group assignment will be generated by random allocation software. The group assignment will be written and placed in an opaque sealed envelope and given to participants by the research assistant after baseline data collection (T_0_). Outcome evaluation will take place at the 6-week intervention (T_1_) and upon completion of the 12-week intervention (T_2_) by trained research assistants who are blinded as to the participants’ intervention allocation (Fig. 1). Participants will not be blinded as to their group allocation. The following parameters for outcome assessment will be used to include health behavior, emotional outcomes, health-related quality of life, cardiac physiological risk parameters and unplanned health services use. Participants’ travel expenses for data collection will be reimbursed.

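### Routing event calls and monthly calls through the outcome assessor adds avoidable risk of unmasking the trial's only blinded role

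*Protocol article*

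**What the plan says.** The Methods section states: "The study design is a single-blinded two-arm parallel randomized controlled trial". Under Randomization and data collection procedure, T1 and T2 outcomes are evaluated "by trained research assistants who are blinded as to the participants’ intervention allocation", and "Participants will not be blinded as to their group allocation". Assessor blinding is therefore the only blinding in the trial. The same section counts unplanned health services use among the outcomes.

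Under Secondary outcomes, that outcome covers unplanned cardiac-related readmissions, emergency department visits and re-vascularization. It is collected by telephone in two ways:

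- By the participant: "the participants will be reminded to call the outcome assessor whenever an unplanned health services event occurs".
- By the assessor: "the outcome assessor will assess participants’ unplanned medical services use by monthly call asking about the detailed date, unit, diagnosis and related information".

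The article gives the lack of an electronic medical records system as the reason for relying on participants' reports.

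**The concern.** The calls put people who know their arm in repeated conversation with the person who is meant not to know it. The subject of the calls invites disclosure. Intervention participants have nurse contacts at weeks 2 and 4, a WeChat group and a platform through which to raise adverse changes in health (Tele-care platform). Someone describing a readmission could easily mention any of these. The last item on the monthly list of questions is open-ended and gives room for it.

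An assessor who has learned the arm could, without intending to, take a tape measurement differently, repeat a blood pressure reading, or probe and classify an event differently. Event classification is the most exposed: the calls themselves collect the outcome, someone must judge whether an event was unplanned and cardiac-related, and the article describes no independent record to check against. The Data analysis section then carries these events into a survival analysis.

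**Working it through.** **1. Is the person on the phone the blinded assessor?** One section speaks of trained research assistants in the plural, the other of the outcome assessor in the singular. The article does not say outright that they are the same people. It does assign outcome evaluation to blinded research assistants and then lists unplanned health services use among the outcomes, so identity is the natural reading. If they are different people, one sentence saying so would largely settle the point for the T1 and T2 measurements.

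**2. Is there a stated safeguard on these calls?** The only instruction to participants about disclosure, under Tele-care platform, concerns other patients in the hospital and is aimed at contamination. It does not cover assessors. Under Process evaluation the article does state that the interviewer is independent of outcome assessment. It makes no such statement about the calls.

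**3. How many monthly calls precede the assessments?** Inputs: 146 participants (Study sample), T1 at 6 weeks and T2 at 12 weeks (Randomization and data collection procedure), monthly calls (Secondary outcomes). The stated 146 reproduces: an effect size of 0.5 with 80% power and two-sided 5% needs 64 per arm by the t-test, so 128 / (1 − 0.12) = 145.5, rounded up to 146. Here it serves only as a count.

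The start of the calls is not given, so I assume they start at entry and that T1 and T2 are timed from the same point.

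- One month = 52 / 12 = 4.33 weeks.
- Calls fall at weeks 4.3, 8.7 and 13.0.
- Before T1 (week 6): one call, 1 × 146 = 146 calls.
- Before T2 (week 12): two calls, 2 × 146 = 292 calls, of which 146 also precede T1.
- With the planned 12% attrition all occurring before the first call: 0.88 × 146 ≈ 128 participants, and 2 × 128 = 256 calls.
- With four-weekly calls (weeks 4, 8, 12), the third falls on T2 itself, so two still precede it.

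Event-triggered calls come on top. The article gives no event rate, so they cannot be counted.

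**4. Which outcomes can the assessor influence?**

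| Outcome | Exposure to an unmasked assessor |
|---|---|
| Pedometer step count | Little; recorded by a device |
| IPAQ, HPLP-II, CSES, MacNew, DASS-21 | Little if self-completed; mode of administration not stated |
| Smoking status | Some if asked by interview |
| Waist circumference | Yes; manual tape, though the site is fixed |
| Blood pressure | Some; device, posture and rest are fixed |
| Unplanned health services use | Yes; probing and classification |

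**5. How large is the bias?** It cannot be derived. The article gives neither a rate of unmasking nor an effect of unmasking on any measure.

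**The case against.** The strongest reply is that any trial with unblinded participants and blinded assessors has such contact, at the latest at the T1 and T2 visits. Having the blinded assessor collect events, and not the intervention nurse, also favours equal ascertainment in both arms. Both points are fair. The choice is defensible, and nothing in the text says that allocation is disclosed. What remains is that these calls are additional and recurring, concern health events, and partly precede the measurements that blinding is meant to protect.

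A second reply is that rosters, call scripts and assessor training belong in the full protocol, which is not shown. This stands for their absence as such. It does not dispose of the routing of the calls, which the article itself fixes.

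A reader might go further in four ways that the document does not support:

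- **That the plan contradicts its own blinding claim.** It does not; it creates a risk to it.
- **That the allocation envelope unblinds the assessors.** It is "placed in an opaque sealed envelope and given to participants by the research assistant after baseline data collection". Nothing says that this person sees the content or later assesses outcomes. A shared job title is not evidence of unblinding.
- **That there are about 440 calls.** That is 3 × 146 = 438, and the third call does not precede T2 on either schedule above.
- **That type I error rises by a stated amount.** Any such figure needs an assumed bias, for which the document offers no basis.

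Nor are the primary outcomes the main issue. They are mostly device-recorded or participant-reported, and the unblinded participant is the larger source of bias there. The Limitations section already concedes social desirability and recall bias.

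**Conclusion.** The point holds as an avoidable risk to blinding. The plan sends event-triggered calls and about two monthly calls per participant before T2 (roughly 290 in all, about half of them before T1) to the outcome assessor. This rests on two assumptions: that this assessor is one of the blinded research assistants, and that calls start at entry. The exposure is mainly in assessor-dependent secondary outcomes (waist circumference, blood pressure, classification of events as unplanned and cardiac-related) and in any items asked by interview, such as smoking status. The size of any resulting bias is unknown. The matter deserves correction because assessor blinding is the only blinding claimed and the remedy is cheap.

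**What to change.** 1. Among the research assistants already planned, have the one who takes a participant's event and monthly calls not perform that participant's T1 or T2 assessment, and state this in the plan.
2. Open every call and every assessment visit with a short scripted request not to mention the study group or programme.
3. Replace the open-ended last item of the monthly call with a structured form limited to date, unit, diagnosis, and whether the event was unplanned, cardiac-related or a re-vascularization. The outcome definition needs those last three.
4. Record at T1 and T2 whether the participant's allocation became known to the assessor, and report it by arm.

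The roster protects the T1 and T2 measurements but not the event outcome itself, because whoever takes the calls still collects it. The script and the form are needed for that.

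The cost is some rostering work, a call script and a short form, with slightly less continuity between participant and assistant. The article mentions several assistants but not how many, so the sponsor should confirm that the roster is workable.
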